## **1. Why a study on HPV vaccine schedules in the province of Quebec?**

### **1.1 HPV and Associated Diseases: General Epidemiological Considerations**

Human papilloma viruses (HPV) infect the skin and mucosae. There are over a hundred types of HPVs, which are identified by numbers(1,2). About forty types of human papilloma viruses can infect the anogenital mucosa. Between 15 and 25(3) of these viruses have been associated with the development of cancerous or precancerous lesions, and as a result, these viruses are known as oncogenic or high-risk viruses(3). HPVs have been associated with cancers of the: cervix, vagina, vulva, anus, penis and certain cancers in the oro-pharyngeal region. HPV types 16 and 18 are respectively the 1st and 2nd viruses most frequently identified in these cancers(4). Together, HPV types 16 and 18 appear to be responsible for about 70% of cervical cancers worldwide(4).

Infection of the genital mucosae by one HPV is very frequent. The lifetime risk of acquiring at least one HPV genital infection has been estimated at more than 70%(5). These infections usually occur in the years following onset of sexual activity(6,7). Transmission mainly results from intimate and prolonged contact with infected skin/mucosa. Most infected persons will clear the infection without sequelae (even those infected with oncogenic viruses)(8). However in a few, infection will persist and might eventually trigger precancerous or cancerous modifications(9–11). Because of its histologic features, the mucosa of the cervix is particularly vulnerable to the oncogenic effect of high risk viruses.

Between 2004 and 2007 in Quebec, there were about 281 new cervical cancers and 69 deaths per year(12). It was also estimated that approximately 131 HPV-associated cancers occurred yearly at other anatomical sites (vulva, vagina, oropharynx...) in Quebec women(12).

### **1.2 Prevention of cervical cancer: screening and vaccination**

Fortunately, precancerous modifications of the cervix evolve towards cancer slowly. The peak of age of new HPV infections occurs between 20 to 24 years of age, that of precancerous lesions at 25-35 years of age and invasive cancers at 50 years(13). Precancerous modifications can be identified by a cytological exam of samples collected at the cervix (Pap test). Women with abnormal Pap test result(s) will be directed to colposcopy for diagnosis. If a precancerous lesion is identified, its treatment will prevent progression to cancer.

Activities related to cervical cancer screening have been in place in Quebec for more than 50 years. These activities, which are opportunistic, had a certain impact on the incidence of and mortality from cervical cancer(13). However, this success is quite expensive given that screening have to begin in the twenties and be repeated every 2 to 3 years till the sixties(14). False positive results cause an important number of unnecessary exams. Additionally, some treatments of precancerous lesions have been associated with an increased risk of premature deliveries and neonatal mortality(15,16). Finally, nowadays, the main reason of cervical cancer related death is a non-use or insufficient use of screening by some women(17). These women mainly originate from the most vulnerable groups, thus raising a question of social equity. Some programs have implemented measures to reach these high risk groups with mitigated results However, it should be noted that up to 40% of women diagnosed with cervical cancer have been screened(18).

In this context, preventing cervical cancer through vaccination is particularly appealing. With a school-based program, we hope to reduce inequities and achieve a higher coverage than that achieved with screening(17,19). Only a few vaccination visits are required and interventions before pregnancy (and their potential impact) are prevented.

There are three HPV vaccines licensed in Canada. The first targets the 2 most oncogenic HPV types (bivalent, targeting types 16 and 18). The second targets these 2 viruses in addition to the 2 main types responsible of genital warts (quadrivalent, targeting types 6, 11, 16 and 18). The third licensed in February 2015 includes the 4 types in the 2nd vaccine in addition to 5 other oncogenic types (31, 33, 45, 52, and 58). The last two vaccines are produced by the same company (Merck) with the same manufacturing process. It is therefore reasonable to think that the nonavalent vaccine will likely replace the quadrivalent vaccine. Many prelicensure studies have compared the nonavalent to the quadrivalent vaccine. The results show that both vaccines generate a similar response against types 6,11,16,18. A 3-dose vaccine schedule is currently licensed for each vaccine (0, 2, 6 months for the nonavalent and quadrivalent vaccines and 0, 1, 6 months for the bivalent). For the 3 vaccines, a vaccine schedule with 2 doses administered 6 months apart is equally licensed in Canada in persons aged 9 to 14 years. These 3 vaccines are also licensed in many other countries, they are highly immunogenic and usually well tolerated(20–24). Randomized controlled trials have demonstrated their efficacy in the prevention of precancerous lesions(25,26). Maximal efficacy is achieved when vaccination is implemented before onset of sexual activity.

The vaccine used in this study is GARDASIL®, which was administered to the girls in the 4th year primary school (4th grade) targeted by this project.

### **1.3 HPV vaccination in Canada and in Quebec**

All Canadian provinces have a school-based HPV vaccination program. In 2008, based on the recommendation of its provincial Advisory Board (Comité sur l'immunisation du Québec, CIQ) Quebec began a school-based vaccination program with Gardasil® and an extended HPV vaccination schedule in 4th grade (0, 6, 60 months) specifying that «the 3rd dose was to be administered ... if deemed necessary». In 2012, most members of the HPV ad hoc committee (which included members of the Quebec Immunisation Advisory Board) renewed the recommendation on the use of the quadrivalent vaccine (Gardasil®). In spring 2013, the CIQ recommended not to administer the 3rd dose scheduled at month 60 and to evaluate (among others) the comparative efficacy and immunogenicity of two vaccine schedules (0, 6 months and 0, 6, 60 months) within a study (the present study)(27) .

Since 2016, in the province of Quebec, the nonavalent vaccine is used and the program offers HPV immunisation free of charge to grade 4 boys and to men who have sex with men (MSM) up to 26 years of age. (28,29).

In September 2018, the Quebec HPV vaccination public program implemented two main changes: 1) a mixed schedule is used in the program for boys and girls aged 9 to 17 years (one dose of nonavalent vaccine and one dose of vaccine bivalent) and 2) HPV vaccination is offered to boys in grade 9 (28).

### **1.4 HPV vaccination: benefit of alternative schedules**

Alternative 2-dose vaccine schedules (e.g. 0, 6 months) offer obvious potential benefits: they can help to have a better acceptability while reducing vaccination-associated costs if further doses confer little or no additional benefit. Moreover, some vaccine schedules can facilitate coadministration with other vaccines. Based on current knowledge and data, it is relevant to consider 2-dose vaccine schedules.

HPV vaccines are very immunogenic and generate antibody titers higher than those conferred by the natural infection(30–32). Additionally, Canadian and Quebec data showed that children aged 9-13 years have a very good immune response. After 2 doses, they achieved antibody titers higher than that achieved in women aged 16-26 years who received 3 doses of vaccine and in whom the clinical efficacy of the vaccine has been demonstrated(33–35). Generally, the peak of antibody titers occurs 1 month following vaccination, then the titers decline during the next months and finally stabilize(36–39).

It might be useful to underscore that no antibody level has currently been identified as a reliable marker of vaccine efficacy. The duration of protection conferred by licensed vaccines is also unknown. Several cost-benefit studies have underscored that duration of protection is one of the key elements for the relevance of HPV vaccination programs(40). Therefore, the administration of a booster dose can be of interest. The administration of a booster dose 5 years after primary vaccination induces higher antibody titers than after primary vaccination. This has been seen with both hepatitis B and HPV vaccines(41,42). With this type of schedule (0, 6, 60 months), the high level of antibodies after the booster dose will occur shortly before the beginning of sexual activity in most youths. The booster will be administered at a time when youths can be reached easily (before they leave school) therefore maximizing the use of resources already in place for the vaccination program(13).

For these reasons, some health jurisdictions have adopted alternative vaccine schedules. In 2010, British Columbia (as well as Mexico) implemented a program similar to the Quebec program, offering the possibility to reconsider the need of a 3rd dose(43). In 2013, British Columbia chose to administer the 3rd dose 3 years after the first 2 doses which were administered 6 months apart (0, 6, 36 months). In 2014, they ceased to give the 3rd dose thus remaining with a 2-dose schedule. In 2017-2018, one Canadian province was using the 3-dose schedule recommended by the manufacturer (0, 2, 6 months) whereas the others adopted the 2-dose schedule (0, 6 months). As of 2012, the Swiss expert committee recommended the implementation of a 2-dose schedule with the 2 doses administered at a 6-month interval(44) and England did the same in 2014(45,46). In 2014, other committees and organizations recommended a schedule with 2 doses administered 6 months apart in preadolescents(47–49). In 2017, around 65% of the worldwide HPV vaccination programs were using a 2-dose schedule(50).

## **1.5 Why is it essential to conduct a study on HPV vaccine schedules in Quebec now?**

To our knowledge, there are currently no data on the comparative efficacy (vaccinated versus unvaccinated) of the originally licensed schedules (0, 1, 6 or 0, 2, 6 months) when administered to preadolescents. There is also no efficacy data originating from studies which used the schedules with 2 doses administered 6 months apart or an extended schedule (0, 6, 60 months). The data from some ecological studies which compared women scheduled to receive 3 doses but instead receive less (1 or 2 doses) were published or presented(51–55) and suggest inconsistent findings regarding the need of the 3rd dose. Some indicate a good protection following the first dose whereas others indicate that protection is inversely proportional to the number of doses received. Because the persons receiving a limited number of doses might have different characteristics and risks factors (in clinical studies non-compliant persons are generally at higher risk of the outcome of interest) interpretation of the results was difficult and this has been highlighted by the authors themselves or by letters to the editor(54).

The research team in charge of an Indian study reported results on comparative efficacy after 1, 2 or 3 doses of Gardasil administered to girls aged 9 to 18 years. The results of this study showed that geometric mean titers (GMT) at 7, 18, 24, 36 and 48 months in the group vaccinated with 2 doses were non-inferior to GMTs observed in the group receiving 3 doses. Antibody avidity at 18 months was similar in the groups vaccinated with 1, 2 and 3 doses. In their conclusion, the authors mentioned that the 2-dose schedule (0, 6 months) was non-inferior to the 3-dose schedule(56–58).

A study using population registries in Denmark evaluated the risk of anogenital warts among 550,690 girls eligible to vaccination between 2006 and 2012. The authors concluded that (1) with the original schedule (0, 2 and 6 months), 3 doses were necessary to achieve complete protection against anogenital warts and that (2) a vaccine schedule with 2 doses administered 6 months apart could be as efficient as the original 3-dose schedule. These results were observed in girls aged less than 16 years as well as in those aged 16 years or more.

Following HPV vaccination, the role of the immune memory in the protection against clinical diseases remains poorly studied(59,60) and we cannot directly extrapolate the immune system's response to a booster dose to the response following an infection, which is generally localised.

As mentioned previously, there are Canadian data on the comparative efficacy of the 0, 6 months and 0, 2, 6 months schedules. There is also a Quebec study which measured the immunogenicity of the 0, 6, 42 months schedule(61,62). To our knowledge, there is no study which will provide comparative data on the immunologic non-inferiority of the 3-dose 0, 6, 60 months schedule compared to the schedule with 2 doses administered 6 months apart. Instead of investigating the role of a booster dose we could theoretically just wait for the occurrence of lesions in vaccinated persons (breakthrough) and then confirm the need for a booster. However, that would entail a functional surveillance system with valid measurements occurring at different time points, which is not the situation in Quebec. Additionally, there can be a long delay from HPV infections to the lesions that can lead to cancer; therefore if we were to discover that duration of protection is shorter than expected it would be too late to intervene. Finally, even if the available tools (e.g. vaccination registry, screening and diagnostic and treatment information) made such a careful follow-up possible, in the scenario where lesions would occur in a higher number of vaccinees than expected, the decision-makers would not have the information on the relevance of an additional dose administered 5 years later nor would they know if this dose can significantly extend the duration of protection. In the absence of other data, they might have to come back to a schedule with 3 doses administered within 6 months.

## **1.6 Overlap between ICI-VPH and the Canadian study (QUEST) comparing a 2-dose schedule (0, 6 months) to a 3-dose schedule (0, 2, 6 months).**

An ongoing Canadian study (QUEST) also aims to compare 2 vaccine schedules (see Appendix A). It is an observational quasi-experimental study which compares the cumulative risk of persistent HPV infections in young girls who received 2 (Quebec, British Columbia) or 3 doses of HPV vaccine (British Columbia, Alberta, Nova Scotia, Prince Edward Island) as part of their provincial school-based vaccination programs. This study does not provide an answer to the question regarding the vaccine schedule that can be used in Quebec: should we administer a 3rd dose at 60 months? Additionally, in the other provinces the vaccinated girls are older (11 – 13 years) than those vaccinated in Quebec (9 – 10 years). Given that only Quebec and British Columbia administered the first 2 doses at a 6-month interval during the recruitment period, Quebec's collaboration is essential to the success of the Canadian project. The data collected from the participants of the 2-dose group described in this protocol will be anonymously shared with the QUEST team. Of note, outcomes and effect measures have been harmonized between the 2 studies in order to facilitate collaboration. Part of the funding of the present study is provided by the Michael Smith Foundation, however most of the funding will be provided by the Quebec ministry of health (Ministère de la Santé et des Services sociaux du Québec, MSSS).

## **2. Objectives**

### **2.1 Primary objective**

To evaluate if a vaccine schedule with 2 doses of Gardasil® administered at a 6-month interval is non-inferior to a schedule with 3 doses administered at 0, 6, 60 months in the prevention of HPV-16 and HPV-18 infections which persist at least 6 months, and this, up to 10 years following the first injection.

### **2.2 Secondary objectives**

a) To compare the antibody geometric mean titers and seropositivity (for HPV types 6, 11, 16, 18) among girls who received 2 doses of Gardasil® (0, 6 months) to the antibody geometric mean titers and seropositivity among girls who received 3 doses of Gardasil® (0, 6, 60 months) and this, 60, 90 and 120 months after the first injection.

b) To evaluate if a vaccine schedule with 2 doses of Gardasil® administered at a 6-month interval is non-inferior to a schedule with 3 doses administered at 0, 6, 60 months in the prevention of HPV-16 and HPV-18 infections which persist at least 6 months, and this, up to **13 years** following the first injection.

c) To compare the antibody geometric mean titers and seropositivity (for HPV types 6, 11, 16, 18, **31, 33, 45, 52 and 58**) among girls who received 2 doses of Gardasil® (0, 6 months) to the antibody geometric mean titers and seropositivity among girls who received 3 doses of Gardasil® (0, 6, 60 months) and this, 60, 90 and 120 months after the first injection.

d) To explore if a vaccine schedule with 2 doses of Gardasil® administered at a 6-month interval is non-inferior to a schedule with 3 doses administered at 0, 6, 60 months in the prevention of condylomas, and this, up to **13 years** after the first injection..

e) To compare the level of persistent HPV infections in the 2 study groups to that observed in retrospective cohorts of unvaccinated girls.

## **3. Proposed study**

### **3.1 Study design**

We propose a non-inferiority randomized trial. The girls who received 2 doses of Gardasil® 5 years ago (see study population section) will be randomly assigned to a «2-dose» group where they will not receive additional doses of vaccines, or to a «3-dose» group where they will receive a 3rd dose of vaccine. The girls and their parents will know the group to which they were assigned. Blood samples will be collected among a subgroup of girls (250 in each of the two groups) in order to determine antibody titers (objectives 2.2.a and c). The persons assessing the primary and secondary outcomes (HPV and antibody testing) and the data analysts (statisticians) will be blinded to group allocation.

### **3.2 Study population**

We will invite girls who initiated vaccination with Gardasil® in 2008, 2009, 2010 and 2011 at 9-10 years old (see explanation in section 3.4), who received 2 doses at a 6-month interval (minimum of 4 months and maximum of 12 months between doses) and are living in the Montreal, Quebec city (Capitale-Nationale) or Saguenay-Lac-Saint-Jean regions at the time of enrolment to participate to this study (the enrolment areas will be defined using the postal codes closest to the participating research centers). The girls will be invited about 5 years after the beginning of

vaccination, in such a way that during fall 2013 we will start inviting the girls who initiated vaccination in the fall 2008 as part of the school-based vaccination program. In 2014, we will invite the girls who initiated vaccination during fall 2009, in 2016 we will invite those who initiated vaccination during fall 2010, and in 2016 we will invite those who initiated vaccination during fall 2011 (see figure on conduct of the study, appendix B).

The only inclusion criteria are:

- To have received 2 doses of Gardasil® at a 6-month interval (minimum of 4 months and maximum of 12 months between doses) in 4th grade in 2008-2009, 2009-2010, 2010-2011 or 2011-2012;
- To understand French or English;
- To give an informed consent (girl and parent);
- To live in one of the targeted regions;
- To not be pregnant at the time of enrolment;
- To not be considered as immunodeficient at the time of enrolment, and at vaccination in 4th grade.

### **3.3 Enrolment**

After approval by the Commission d'Accès à l'Information we will contact the Quebec health insurance board (Régie de l'Assurance Maladie du Québec, RAMQ) in order to obtain the contact information of girls aged 9 years on September 30th, 2008 (i.e. born between October 1st, 1998 and September 30th, 1999 for the first enrolment year), 9 years on September 30th, 2009 (i.e. born between October 1st, 1999 and September 30th, 2000 for the second enrolment year), 9 years on September 30th, 2010 (i.e. born between October 1st, 2000 and September 30th, 2001 for the third enrolment year), 9 years on September 30th, 2011 (i.e. born between October 1st, 2001 and September 30th, 2002 for the fourth enrolment year).

From September 2013 to June 2014 we will contact the girls' parents by mail to invite those who received 2 doses of Gardasil® during the 2008-2009 academic year. The letter will explain the purpose of the project, how it will be carried out and details on inclusion criteria. This same step will be carried out in 2014, 2015 and 2016.

A phone number and an e-mail address will enable parents to contact a research nurse (1) to obtain further information, (2) to check eligibility and (3) to take an appointment with a research nurse at the coordinating center.

During this appointment, the research nurse will confirm the participant's eligibility, will obtain informed consent from the girl and her parent, will perform a urine pregnancy test on the girl and will randomize her to one of the groups, administer the 3rd dose if she was assigned to the «3rd dose» group and collect the blood sample if she is part of the subgroup targeted by the secondary objective on immunogenicity. A financial compensation will be offered to the girl and parent 20,00\$ each) for this face-to-face appointment. The participant will collect the first HPV vaginal sample after receiving explanations on the self-sampling procedure and will fill the first questionnaire. A financial compensation will be provided for each self-sampling kit received (5,00\$ per sampling, then 10,00\$ per sampling when the girl turns 18 years of age).

### **3.4 Conduct of the study**

After the first visit, the girls will have to perform vaginal self-samplings every 6 months and fill an online questionnaire once a year. They will receive an e-mail or a text message (SMS) 2 weeks before the target date. The self-sampling kits will be sent by mail. A reminder (e-mail or SMS) will be sent if the tube is not returned or the questionnaire not filled 2 weeks after the target date. A

second reminder (e-mail, SMS or phone call) will be made 2 weeks later (i.e. 1 month after the target date).

The 500 girls included in the immunogenicity aspect of the study will be seen at the coordinating center 90 and 120 months after the first injection, in order to collect blood samples which will be used to measure presence and titers of antibodies against HPV. Because there were less losses to follow-up than expected, and in order to reduce the costs as much as possible while being able to meet the secondary objective on immunogenicity, the blood sampling at month 90 will be performed in only 350 participants (175 per group). Section 3.8.2 specifies the number of participants required at the end of the study to reach the statistical power needed for this objective.

## **3.5 Study variables and effect measures**

### **3.5.1 Intervention: definition and measurement**

The main variable of interest is the number of Gardasil® doses received. It will be determined experimentally and will only have 2 possible values: 2 doses or 3 doses, the 3rd dose being the one administered by the research nurse during the face-to face-appointment. In order to have non-inferiority estimates as conservative as possible, a «per protocol» approach will be used during analyses as recommended for non-inferiority randomized trials(63). Participants who did not receive the number of doses planned in the protocol will be excluded from this analysis. This number will likely be limited given that the 3rd dose is given immediately after randomization. The experience with the school-based program show that very few girls randomized to the «2 doses» would have already received a 3rd dose (or more) out of the provincial public vaccination program (e.g. paying for an additional dose at a CLSC or a medical clinic during the 4 years following administration of the 2 first doses in 4th grade) ([name]'s personal communication, source: VAXIN database, Capitale-Nationale region). Girls will be regularly questioned on the subject and will be excluded from the per protocol analysis in case they have received an off-protocol dose of Gardasil®, Gardasil® 9 or Cervarix®. However, an intention-to-treat analysis will equally be performed and will include them (see section 3.9 analyses).

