### 3.9 Analysis

Descriptive analyses will be used to describe the participants and compare the two study groups. Specifically, the following analyses will be performed for each of the objectives mentioned in section 2.

For the primary objective:

A survival analysis (time to event analysis) will be performed in order to answer the main study questions. This approach will take into consideration the different duration of follow-up resulting from the fact that the date of entry in the cohort will vary between participants. Time 0 will be defined as the date of randomization. The time of event will be defined as the first occurrence of a persistent infection. Participants with no persistent infection will be censored (right-censored) at: (a) loss to follow-up, (b) death or (c) end of the study whichever comes first. The preliminary analyses will include the comparison of the Kaplan-Meier curves using a non-parametric test (*log-rank test*, *Wilcoxon*) describing how the proportion of participants developing a persistent infection varies over time in each group. The main non-inferiority analysis will rely on the Hazard ratio's (HR) 95% confidence interval. Adjusted analyses will take into consideration the potential confounding factors collected with the annual questionnaire. If the HR's upper limit is not higher than 1.05 (representing a 5% difference of efficacy between the two schedules), we will conclude to a non-inferiority of the 2-dose calendar.

This analysis will then be repeated with the « intention-to-treat » method to evaluate the differences generated by a change in the exposure's definition. Sensitivity analyses will also be performed to evaluate the impact of modifying the outcome's definition. Indeed, it is likely that some girls will not exactly respect the vaginal self-samplings' schedule. We will vary the primary outcome's definition (e.g. consider as persistent infection only if the sample were consecutive and 6 months apart, or

consider as persistent infection a situation where the same type of virus was identified in two consecutive samples regardless of the number of months between the samples).

For the secondary objectives on immunogenicity (objectives 2.2.a and c), two analyses will be performed to measure non-inferiority at month 120:

1) An intention-to-treat analysis (*ITT analysis*) in which all the serologic results available will be included.

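### The primary per-protocol set drops a girl entirely for an off-protocol HPV dose at any time, so earlier valid follow-up and infections are deleted and the hazard ratio can be biased in either direction

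*Protocol*

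**What the plan says.** Section 3.5.1 chooses per protocol as the main approach with the aim stated as "In order to have non-inferiority estimates as conservative as possible". Two exclusions follow. The first is "Participants who did not receive the number of doses planned in the protocol will be excluded from this analysis". The second covers extra doses obtained outside the study: "Girls will be regularly questioned on the subject", and they "will be excluded from the per protocol analysis in case they have received an off-protocol dose of Gardasil®, Gardasil® 9 or Cervarix". No time limit is attached, and the second rule is not confined to one group.

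Section 3.9 sets time 0 at randomization and the event at the first persistent infection. It then says "Participants with no persistent infection will be censored (right-censored) at" loss to follow-up, death or end of study, whichever is earliest. An off-protocol dose is not on that list.

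Intention-to-treat is the second analysis. Section 3.5.1 says "However, an intention-to-treat analysis will equally be performed and will include them", and section 3.9 says "This analysis will then be repeated with the « intention-to-treat » method".

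**The concern.** Exclusion is defined by something that can happen years after time 0. A girl with a persistent HPV-16 infection in year 2 and an extra dose in year 4 had her infection while on her assigned schedule, yet the rule removes both the infection and the four years of valid follow-up. That is selection on a future event.

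At stake is the primary estimate. The trial plans on very few infections, so a handful of exclusions that depend on outcome or risk can move the hazard ratio noticeably. Because nothing controls the direction, the rule does not secure the conservative estimate for which the per-protocol set was chosen.

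**Working it through.** **1. Does the rule cover doses after randomization?** Yes, for two reasons.
- Section 3.5.1 provides for repeated questioning.
- It names Gardasil 9, which section 1.2 says was licensed in February 2015. Section 4.3 has the first cohort randomized from September 2013 to June 2014. For that cohort, a dose of the licensed product could only come after time 0.

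The reassurance in section 3.5.1 that exclusions will be few concerns the third dose given at once after randomization and doses bought before randomization. It does not address doses during follow-up.

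**2. The plan's own figures** (section 3.8.1, Tables 2 and 3). Inputs: 1667 recruited per group, yearly losses of 1% to 5%, 5-year cumulative incidence without vaccination 15.02%, efficacy 95% (3-dose) and 94% (2-dose).
- Effective size: 1667 × 0.99 × 0.98 × 0.97 × 0.96 × 0.95 = 1431, as stated.
- 3-dose events: 1431 × 0.1502 × 0.05 = 10.7.
- 2-dose events: 1431 × 0.1502 × 0.06 = 12.9.
- Total 23.6, against the 23 stated. Planning hazard ratio 12.9/10.7 = 1.20.

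**3. Effect of deleting events.** Whole numbers, equal group sizes, HR ≈ d2/d3, upper 95% limit ≈ HR × exp(1.96 × √(1/d2 + 1/d3)).

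| Events (2-dose v 3-dose) | HR | Upper limit |
|---|---|---|
| 13 v 11 | 1.18 | 2.64 |
| 12 v 11 | 1.09 | 2.47 |
| 11 v 11 | 1.00 | 2.31 |
| 10 v 11 | 0.91 | 2.14 |
| 13 v 10 | 1.30 | 2.97 |
| 13 v 9 | 1.44 | 3.38 |

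One deleted 2-dose event lowers the HR by 1/13, about 8%. One deleted 3-dose event raises it from 1.18 to 1.30, about 10%.

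**4. Direction under full exclusion.** Let u_n be uptake of an off-protocol dose among uninfected 2-dose girls and u_i uptake among infected ones. Suppose there is none in the 3-dose group. The per-protocol 2-dose risk is p(1−u_i) / [p(1−u_i) + (1−p)(1−u_n)], with p = 0.1502 × 0.06 = 0.00901. Dividing by the 3-dose risk, 0.1502 × 0.05 = 0.00751, gives the ratio. Example with u_n = 5% and u_i = 10%: 0.00811 / (0.00811 + 0.94144) = 0.00854, and 0.00854/0.00751 = 1.137.

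The uptake values are assumptions; the protocol gives none.

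| u_i / u_n | 0.5 | 1 | 2 | 3 | 5 |
|---|---|---|---|---|---|
| u_n = 5% | 1.231 | 1.200 | 1.137 | 1.075 | 0.949 |
| u_n = 10% | 1.266 | 1.200 | 1.068 | 0.935 | 0.669 |

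The ratio stays at 1.20 when uptake is unrelated to infection, falls when infected girls take the dose more often, and rises when they take it less often.

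**The case against.** The strongest reply is that the rule has not been shown to help the 2-dose schedule. A reader might infer that it favours non-inferiority, because allocation is open and girls at higher risk might seek another dose. The protocol does not support that step. It gives no uptake by group or by infection status, and the exclusion applies to both groups. Some suggested triggers also fit badly: section 1.2 has screening starting in the twenties, while Table 2 has primary follow-up running from about age 15 to 20, and it attributes genital warts mainly to types other than 16 and 18. The protocol does not say that girls learn their HPV results. This part of the objection stands.

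Deletions may also be few. One expected deletion needs about 1/12.9 = 8% of infected 2-dose girls to take a later dose, and three need about 23%. Table 2 puts (15.02 − 6.10)/15.02 = 59% of the 5-year incidence in the last two years, which leaves little time for a dose after the infection. This limits the likely size but does not remove the fault.

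Intention-to-treat brings the deleted events back, so a discrepancy would be visible. It does not repair the primary analysis, because it also counts follow-up after the extra dose as 2-dose time. Neither planned analysis uses exactly the follow-up spent on the assigned schedule.

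Removing time after an extra dose is indeed conservative compared with intention-to-treat. Censoring at the dose keeps that advantage without discarding what came before.

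Finally, such detail might be left to an analysis plan. Here, however, the protocol itself fixes exclusion of the girl and lists the censoring reasons.

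**Conclusion.** The point holds as a fault in how the primary set is defined. The stated rule selects on a future event and deletes valid follow-up and infections on the assigned schedule. Bias can go either way, and a claim that it favours non-inferiority would go beyond the documents.

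The size is conditional on unknown uptake. Each deleted 2-dose event lowers the hazard ratio by about 8% on the planned 13 against 11; one, two or three deletions take it from 1.18 to 1.09, 1.00 or 0.91. From that starting point no conclusion changes: every upper limit in the event-deletion table exceeds both the 1.05 of section 3.9 and the ratio of 2.0 implied by the efficacy margin in section 3.8.1 (10%/5%). A change is possible elsewhere. At 11 against 11 the upper limit is 2.31; with two 2-dose events deleted, 9 against 11 gives 0.82 × exp(1.96 × √(1/9 + 1/11)) = 1.97, which crosses 2.0, though not 1.05.

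The relevant exposure is about 5 years from randomization, since the primary objective ends 10 years after the first injection. The longer follow-up of the early cohorts in section 7 serves secondary objectives and should not be used to enlarge this concern. The change should be made, but it is not critical.

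**What to change.** - In section 3.5.1, exclude from the per-protocol set only girls with an off-protocol HPV dose before randomization, or who did not receive their assignment at the randomization visit.
- For a later off-protocol dose, keep the girl, censor her at the date of that dose, and retain earlier follow-up and events. Add this to section 3.9 as censoring reason (d).
- State in advance how an infection is counted when its two positive samples fall on either side of the dose date. Section 3.5.2 allows 5 to 15 months between them, so this can arise.
- Keep full exclusion as a sensitivity analysis, and report the number of girls and of infections excluded, by group.

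The cost is a few sentences and one derived date; girls are already asked about extra doses, so mainly the date needs to be recorded. The downside is that censoring at the dose may be mildly informative if dose-seeking follows risk. The planned intention-to-treat analysis serves as a check on that.
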